#### Aim 3: Integrating the outcomes of the structural and individual-level interventions

We will estimate the joint effect of the structural and individual-level interventions on the percentage of HIV-positive men who are effectively treated (tested, linked to care, and maintained with undetectable VL) by estimating the percentage of HIV-positive men who have been tested in male-centered mobile HTS versus control arms using data on HIV testing and HIV status of the post-intervention assessment participants from Aim 1, and estimating success rates of undetectable VL in SOC and POC + PLC arms in Aim 2 (adjusted for attrition if needed). These estimates will be multiplied to estimate overall success rates of undetectable VL among HIV-positive men in all four combinations of the two interventions. Confidence intervals will be also calculated. We will assume that the interventions do not interact with each other since each targets a different stage in the process leading to successful HIV treatment of HIV-positive men. Given population size and HIV prevalence, we will be able to estimate the number of men who would be identified, treated, and maintained on treatment under each of the possible intervention combinations. A sensitivity analysis will be performed to evaluate the impact of potential non-independence of intervention effects.

A full factorial design is not feasible because one of the interventions is applied at the community level and the other at the individual level; success at the first of the interventions (being tested) is a condition of enrolment into the other intervention. This brings bias into the randomization of the community-level intervention. This design could only be conducted by randomizing whole communities to the four combinations of the interventions, but that would be too costly.

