#### Male-focused and delivered mobile HTS (Component 2)

The mobile HIV-testing services teams coordinate with CBM teams to ensure that testing happens according to the testing schedule. Copies of the testing schedule are distributed to community working groups, community-based outreach volunteers, local police stations, local health centers, and other community centers deemed appropriate by the study team.

Two HTS teams (four male nurse counselors and one driver per team) deliver easy-to-access mobile HIV testing through two mobile caravans. A mobile HTS team circulates through a range of male-centered locations in the community on a regular schedule of days and times suitable for men. Two teams serve the four intervention communities, with each team being responsible for two intervention communities over the course of the intervention. The team is supervised by a Counselor Supervisor.

CBMs are stationed in the vicinity of the men-centered spaces and engage men individually and in groups about the study. Mobilizers also inform men that a small incentive of R50 cell phone airtime (approximately US$5) would be received at completion of testing, regardless of HIV status. Other men in the vicinity of the mobile facility, but not necessarily frequenting the venues, are also encouraged to test by study staff. Recruited men are handed over to the study counselor at the mobile caravan for a fuller explanation of the study, informed consent, and completion of the HTS process.

Participants give consent for on-site POC procedures for screening for HIV and non-communicable diseases (NCDs) using rapid and POC tests. No specimens are retained for HIV and NCDs testing. In the event of a discordant HIV test result, a Dry Blood Spot (DBS) specimen will be collected from the participant for a laboratory confirmatory test to confirm serostatus. No specimens are retained for confirmatory tests. Participants who are eligible for enrolment (HIV-positive and not on antiretroviral treatment) and who consent to enrolment provide a DBS for baseline VL measures. Consent is provided for participants to be re-contacted at three and six months for study contact visits and for an exit visit at nine months after enrolment where participant exit survey data and end-line VL will be collected. Participants consent for their data to be stored and for secondary use of their data if such use is approved by the REC.

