#### HIV testing

HIV testing is conducted using blood collected by finger-stick with a sterile lancet and using a serial testing algorithm for rapid testing according to 2015 South African National HIV Test Services guidelines [75]. All specimens are first tested with one assay (Test 1 or screening test) and specimens that are non-reactive are considered HIV-negative and reported as such. Any specimens that are reactive on the first assay (Test 1) are tested again using a different assay (Test 2 or confirmatory test). For specimens that are reactive on both the first and the second assays, results are reported as HIV-positive. Specimens that are reactive on the first assay but non-reactive on the second assay will receive an ELISA laboratory test and be recorded as discordant. In the case of discordant results, the individual is given the schedule of mobile HTS testing locations and asked to return in seven days [7] for their HIV results.

Participants are triaged according to their HIV test result. HIV-negative participants will have completed their visit, as they are not eligible for further study participation and, if required, referrals to relevant services are made. Study counselors will explain to HIV-positive men in the intervention communities that they are eligible for the randomization and the next phase of the study, if interested. All HIV-positive participants are asked for locator information (addresses and alternate/additional contact phone numbers) so if randomized into the PLC arm they can be contacted. Permission is obtained to call and/or text the participant to arrange and keep in contact for PLC.

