#### Primary outcomes

Proportion of men getting tested for HIV in the last 12 months. This is to find out how many men have been tested for HIV in the last 12 months.

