#### Measurement of Aim 1 outcomes

Conduct post-intervention assessments in intervention and control communities (n = 1600, 8 communities × 200).
Post-intervention random survey data (focusing on self-reported testing history, other wellness-related data, health-seeking indicators, etc.); and specimen samples from men living in the study communities. We will be able to look at reported HIV status versus actual status.

Aim 2: Outcome measures compare enrolled participants assigned to PLC to those in standard care during the intervention.

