## Trial status

Screening and recruitment for the trial began on 30 August 2017. As of 30 November 2018, the study team has been in the field for 15 months with 4473 participants screened (4179 screened for NCDs and tested for HIV, 88 tested for HIV only, and 206 screened for NCDs only). A total of 249 participants have been enrolled for the personalized linkage to care intervention trial within the study. It is expected that enrolment will continue until 30 April 2020.

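### The Aim 3 product multiplies a testing rate among all HIV-positive men by a success rate measured only in men not on ART, so it is not the percentage of all HIV-positive men effectively treated

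*Protocol article*

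**What the plan says.** The target of Aim 3 is the "percentage of HIV-positive men who are effectively treated (tested, linked to care, and maintained with undetectable VL" (protocol article, Data analysis, Aim 3).

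The first factor is the percentage tested in each community arm, estimated "using data on HIV testing and HIV status of the post-intervention assessment participants from Aim 1". Under Measurement of Aim 1 outcomes, that survey is a random sample of 1,600 men, 200 from each of the eight communities, with "specimen samples from men living in the study communities". Nothing restricts it by ART status. The Aim 1 outcome is the "Proportion of men getting tested for HIV in the last 12 months"; the Aim 3 section does not say whether its own testing measure uses the same window.

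The second factor is the rate of undetectable viral load in each Aim 2 arm. Aim 2 draws on a narrower group. The section on mobile HTS (Component 2) describes "Participants who are eligible for enrolment (HIV-positive and not on antiretroviral treatment". The HIV testing section says counselors will explain to "HIV-positive men in the intervention communities that they are eligible for the randomization".

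The combination rule is: "These estimates will be multiplied to estimate overall success rates of undetectable VL among HIV-positive men in all four combinations of the two interventions". The same section then uses population size and HIV prevalence to project the number of men identified, treated and maintained on treatment under each combination. It assumes that the two interventions do not interact, plans a sensitivity analysis for dependence between their effects, and allows an attrition adjustment of the Aim 2 rates. The secondary analyses for Aim 2 add a comparison of HIV-positive men who do and do not enrol.

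**The concern.** A product of the form P(tested) × P(success | tested) is valid only if the second factor describes the men counted as tested in the first. Here it does not.

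A man already on ART with suppressed virus has been tested, linked and maintained, so he meets the target definition. If he did not test within the survey window, the product counts him as a failure. If he did, it gives him the success rate of an untreated man, and a linkage benefit that he could not receive because he is not eligible for Aim 2.

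Aim 3 is one of the three stated aims, and its rates are carried into projected numbers treated. If the label stays as it is, a rate that leaves out the existing treated population will be read as population coverage of effective treatment.

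**Working it through.** **The plan's own figures.** Aim 3 states no number. The planning rates it would use come from the power sections, which reproduce closely:
- Aim 2, log odds ratio test, 175 per arm: 88.2% power at 1/3 against 1/2 (odds ratio exactly 2.0) and 89.4% at 33% against 50%, where the plan states 88%. For attrition, 175 / 0.8 = 219, where the plan states 220.
- Aim 1, simulated Welch test with between-community variance 0.007 plus binomial sampling: 0.044, 0.369, 0.846 and 0.955, where the plan states 0.05, 0.36, 0.86 and 0.95.

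The power statements are not at fault.

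**Inputs.**
- Testing t = 30% (control) and 60% (intervention), from the Aim 1 power section. These are rates for all men, used here for HIV-positive men.
- Success s = 33% (standard of care) and 50% (POC + PLC), from the Aim 2 power section.
- A = share of HIV-positive men already on ART, and v = their suppression. **Both are assumed.** A = 20% and v = 85% give A × v = 17%, the upper bound in the Background for HIV-positive people in South Africa who reach suppression. The Background also speaks of doubling ART coverage to 35%–40%, which implies a starting level of 17.5% to 20%.
- r = testing rate among men on ART; u = testing rate among men not on ART.

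**Algebra.** The survey testing rate is t = A·r + (1−A)·u.
- Planned product: P = [A·r + (1−A)·u]·s
- Target: T = A·v + (1−A)·u·s
- Error in level: P − T = A(r·s − v), negative whenever v > r·s
- Error in joint effect: A(r1·s1 − r0·s0), with 1 = both interventions and 0 = neither. It is zero if men on ART do not retest (r1 = r0 = 0). It is positive if they do, provided r1 ≥ r0 and s1 > s0.

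**Planned product.** 0.30 × 0.33 = 9.9%; 0.30 × 0.50 = 15.0%; 0.60 × 0.33 = 19.8%; 0.60 × 0.50 = 30.0%. Joint effect: 30.0 − 9.9 = 20.1 points.

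**Split by ART status, A = 20%, v = 85%.**
- *Men on ART test as often as others* (r = u = t): 0.17 + 0.8 × 0.099 = 24.9%; 0.17 + 0.8 × 0.300 = 41.0%; joint effect 16.1 points. Check: 0.2 × (0.300 − 0.099) = 4.0 points, and 20.1 − 4.0 = 16.1.
- *Men on ART do not retest* (r = 0, so u = t / 0.8 = 37.5% and 75%): 0.17 + 0.8 × 0.375 × 0.33 = 26.9%; 0.17 + 0.8 × 0.75 × 0.50 = 47.0%; joint effect 20.1 points.

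**Range over A, v = 85%** (neither intervention / both / joint effect):

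| A | Planned product | Equal testing | No retesting on ART |
|---|---|---|---|
| 0% | 9.9% / 30.0% / 20.1 | 9.9% / 30.0% / 20.1 | 9.9% / 30.0% / 20.1 |
| 10% | 9.9% / 30.0% / 20.1 | 17.4% / 35.5% / 18.1 | 18.4% / 38.5% / 20.1 |
| 20% | 9.9% / 30.0% / 20.1 | 24.9% / 41.0% / 16.1 | 26.9% / 47.0% / 20.1 |

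**If tested means ever tested**, every man on ART counts as tested (r = 1). At A = 20% the level error is 0.2 × (0.33 − 0.85) = −10.4 points under standard of care and 0.2 × (0.50 − 0.85) = −7.0 points under POC + PLC. The joint effect is overstated by 0.2 × 0.17 = 3.4 points. The mismatch remains.

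**The case against.** **The joint effect may be unbiased.** If men on ART do not retest, their contribution A·v is the same in all four cells and cancels from every difference. This stands. A reader might infer that the joint effect is necessarily overstated; the documents do not support that, because they give no retesting rate for treated men.

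**The size can be made to look larger than the documents allow.** With 50% on ART and 85% suppressed, equal testing gives 47.4% against 57.5%, a joint effect of 10.1 points, half the planned product. But 0.50 × 0.85 = 42.5% suppressed sits far above the Background's figure of under 17%. A halved effect is therefore not a supported reading.

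**Enrolment counts prove little.** The Trial status section reports: "A total of 249 participants have been enrolled for the personalized linkage to care intervention trial within the study". It also gives 4,179 + 88 = 4,267 men tested. Applying the area prevalence of 31% gives about 1,323 positives and an enrolment share of 249 / 1,323 = 19%; an assumed 15% gives 249 / 640 = 39%. A reader might infer that Aim 2 is unrepresentative. Prevalence among men using the vans is not stated, however, and those not enrolled mix men excluded for being on ART with eligible men who declined.

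**Safeguards exist.** Applying the van-recruited standard-of-care rate to control communities, where men test at facilities, follows from the declared no-interaction assumption, and the planned sensitivity analysis bears on it in part. None of the safeguards reaches the ART mismatch, which is present even with no interaction. The attrition adjustment concerns men already enrolled, and the comparison of enrolled with non-enrolled men is descriptive and does not enter the product.

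**A condensed article may leave detail to the analysis plan.** That would answer an omission. Here the article states the rule and names the population to which the result applies, and the two do not match. It is fair to add that Aim 3 carries no hypothesis test or power claim.

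**Conclusion.** The point holds for the level and, conditionally, for the joint effect. Followed as written, the rule does not estimate the percentage of all HIV-positive men effectively treated, unless no HIV-positive man is already on ART or v happens to equal r·s.

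At A = 20% and v = 85%, the level is too low by 15.0 points with neither intervention and 11.0 points with both under equal testing, and by 17.0 points in each if men on ART do not retest. The joint effect is overstated by between 0 and 4.0 points across those two cases.

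These sizes rest on assumed A and v, on planning rates for all men applied to HIV-positive men, and on the same suppression among men on ART in all four cells. Because 17% is an upper bound and is not specific to men, A × v may be smaller and the error with it. Aims 1 and 2 are unaffected.

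**What to change.** Estimate each of the four cells as the sum of two strata:
1. the share of HIV-positive men on ART times their suppression, common to all four cells; plus
2. the share not on ART, times P(tested | HIV-positive, not on ART) by community arm, times Aim 2 success by individual arm.

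Take ART status from the post-intervention survey, adding one item if it is not already there. The item should establish whether ART began before the intervention period, because a man on ART at the survey may have been put there by the intervention itself. State which testing window Aim 3 uses, and apply the same strata to the projected numbers treated.

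At minimum, relabel the product and the projections as applying to HIV-positive men not on ART. That label is exact only if the testing factor is also computed in those men.

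Extend the planned sensitivity analysis to a range of standard-of-care success for clinic-tested men in control communities.

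The cost is a change of analysis wording, at most one survey item, and a wider confidence interval.

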#### Cost-effectiveness analysis

We will examine effectiveness in terms of: (1) behavioral changes resulting from HIV testing and counseling (which reduces HIV transmission and acquisition); (2) increases in life-expectancy and quality of life from engagement and retention in care; and (3) reductions in HIV transmission, and thus morbidity and mortality from downstream infections, derived from reduced HIV infectivity of those on ART. We will contrast standard of care versus exposure to (1) male-centered mobilization + mobile HTC and (2) combined POC CD4 + personalized linkage to care. For each, we will use Bernoulli-Process models for HIV transmission, extension of life, and enhancement of quality of life.

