### Study aims

The study combines the best of three strategies (male-focused mobilization, community-based mobile HTS, and a small incentive) to determine if the strategies singly and in combination can result in more men diagnosed with HIV and more men linked to and maintained in care with undetectable VL. The specific aims are listed below.
Aim 1: To test the hypothesis, in a cluster-randomized design, that men-centered mobilization and testing strategies plus a small incentive will result in a substantially higher proportion of men getting tested for HIV (difference at least 30%).Aim 2: To test the hypothesis, in an individual randomized design, that POC CD4 testing combined with personalized linkage to care (PLC) will result in a higher proportion of HIV-positive men linked to and maintained in care with undetectable VL than POC alone and that both will be superior to standard of care.Aim 3: To integrate the outcomes of the structural and individual-level interventions and evaluate the joint effect of the structural and individual-level interventions on the percentage of HIV-positive men who are effectively treated (tested, linked to care, and maintained with undetectable VL).

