#### Cluster-randomized study

Eight communities of approximately 5000 persons (four intervention and four control communities) from the GEA and Vulindlela regions will be selected with an equal mix of rural and peri-urban communities to ensure greater generalizability of the intervention in different settings. Each of the communities will be randomized to either men-centered mobilization and testing strategies plus a small incentive or the control condition. Randomization will be performed by the statistical center in a restricted way, so that four communities are assigned to each arm. Randomization code will be written in R and will use the Mersenne-Twister random number generator with seed derived from current system time.

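### The cost-effectiveness section plans no contrast for the combined strategy and does not say on which testing background POC CD4 plus linkage support is compared

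*Protocol article*

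**What the plan says.** The Cost-effectiveness analysis section names its comparators: "We will contrast standard of care versus exposure to (1) male-centered mobilization + mobile HTC and (2) combined POC CD4", with personalized linkage to care completing item (2). The word combined there ties POC CD4 to PLC; it does not tie (1) to (2). The next sentence treats the items one at a time: "For each, we will use Bernoulli-Process models for HIV transmission, extension of life, and enhancement of quality of life".

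The Study aims section puts the question more widely: "to determine if the strategies singly and in combination can result in more men diagnosed with HIV". The Discussion repeats this objective. Aim 3 then combines the Aim 1 and Aim 2 results: "These estimates will be multiplied to estimate overall success rates of undetectable VL among HIV-positive men in all four combinations of the two interventions". It also plans the numbers of men identified, treated and kept on treatment under each combination, and a sensitivity analysis for interventions that do not act independently.

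Standard of care has two meanings in the article. Under Control communities it is testing at health facilities. Under HIV standard of care it is referral of men who have already tested positive and been randomized. Those men come from the mobile service (Individual randomized study), and it is HIV-positive men in intervention communities who are told they are eligible (HIV testing).

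**The concern.** The trial asks whether the two interventions work alone and together, and the joint effect has an aim of its own. The economic section stops at two separate comparisons with standard of care. A health authority deciding whether to fund both, or to add linkage support to a mobile testing programme, would find no planned comparison that answers it.

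The second comparison is also not fully defined. The effect of POC CD4 plus PLC is observed only among men reached by mobile testing, whereas standard of care can mean either usual facility testing or ordinary referral after mobile testing. The two bases give different gains per HIV-positive man in the community and bring different costs into the comparison. If the base is left open, it can be chosen after the results are known.

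**Working it through.** The cost-effectiveness section states no cost, effect or ratio, so there is no figure of the plan to reproduce. The check applies Aim 3's own rule to the article's planning rates.

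**Inputs**
- Tested, standard: 30% (Power calculations for Aim 1).
- Tested, intervention: 60%, the alternative given power 0.86 (same section). The range 40% to 60% is also shown; 40% is the null value there.
- Linked with undetectable viral load: 33% under standard referral, 50% under POC + PLC (Power calculations for Aim 2).
- Assumption, not in the article: testing rates planned for all men apply to HIV-positive men.

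**Rule (Aim 3):** effectively treated = proportion tested × proportion successful.

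| Strategy | Calculation | Effectively treated |
|---|---|---|
| Neither | 0.30 × 0.33 | 9.9% |
| (1) only | 0.60 × 0.33 | 19.8% |
| (2) only | 0.30 × 0.50 | 15.0% |
| (1) + (2) | 0.60 × 0.50 | 30.0% |

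**Gains**
- (1) over neither: 19.8 − 9.9 = 9.9 points.
- (2) on standard testing: 15.0 − 9.9 = 5.1 points.
- (2) on top of (1): 30.0 − 19.8 = 10.2 points.
- Both over neither: 30.0 − 9.9 = 20.1 points.

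**Range for (2) on top of (1)**, which is the intervention testing rate × (0.50 − 0.33):
- at 40% tested: 0.40 × 0.17 = 6.8 points
- at 50% tested: 0.50 × 0.17 = 8.5 points
- at 60% tested: 0.60 × 0.17 = 10.2 points

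Against 5.1 points on standard testing, the gain of (2) is thus 1.3 to 2 times as large (6.8/5.1 to 10.2/5.1).

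**From gain to ratio.** The article gives no costs, so the ratios cannot be computed. If every cost of (2) arose per man enrolled, cost and gain would rise together and the ratio for adding (2) would be the same on both backgrounds. Any cost that does not rise with the number of men found, such as weekly evening clinic sessions might be, would make the ratio depend on the background. The ratio for the combination against neither involves the costs of both interventions and the 20.1 points. Neither listed contrast reports it.

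**The case against.** The best defence is that this is a short summary of a secondary economic model, that the phrase joining (1) and (2) is not wholly unambiguous, and that nothing is out of reach, because Aim 3 supplies the effect estimates for every combination. The two contrasts can also be read as successive steps. Aim 2 men are found by the mobile teams, so (2) adds 10.2 points to the 9.9 points of (1), and 9.9 + 10.2 = 20.1 is the joint gain.

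Much of this stands. It rules out saying that the plan cannot evaluate the combined strategy; it only does not plan to. It does not remove the point. The article lists its comparators instead of leaving them to another document, the list is treated item by item, and the section never states that (2) is a step on top of (1).

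Two stronger readings are tempting and unsupported. First, a reader might infer that the incentive's cost is left out, since the economic section does not name it. But the package is randomized as a single arm: "Each of the communities will be randomized to either men-centered mobilization and testing strategies plus a small incentive or the control condition". The airtime is delivered within Component 2. Study outcomes and Aim 3 also describe the package without naming the incentive, and the economic section lists no cost item for any component. The wording is most naturally shorthand.

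Second, a reader might add the separate gains, 9.9 + 5.1 = 15.0, and conclude that the plan understates the joint 20.1. The article never proposes that sum, and it arises only if (2) is valued on standard testing.

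**Conclusion.** The point holds as a mismatch between the stated economic contrasts and the trial's own objective, together with an undefined base for the second contrast. On the planning rates the gain of (2) is 5.1 points on standard testing and 10.2 points on top of (1), a twofold difference that narrows to 1.3-fold if the intervention testing rate is only 40%. This rests on Aim 3's product rule with no interaction, on all-men testing rates applying to HIV-positive men, and on planning values instead of results. How far the cost-effectiveness ratio moves cannot be stated without costs.

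It is a minor matter. No primary outcome, test or sample size is affected, and the effectiveness inputs for a complete comparison are already planned.

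**What to change.** In the Cost-effectiveness analysis section, replace the two contrasts with the four strategies of Aim 3: standard of care, (1), (2), and (1) + (2). Take effectiveness from the Aim 3 estimates, order the strategies by cost, and report incremental ratios between successive non-dominated ones. This states the testing background for (2) in each comparison and gives the combination its own result. Aim 3's planned sensitivity analysis for non-independence can be carried into the model, since the combinations rest on the same assumption.

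The cost is one more model comparison. It needs no new trial data and does not change the primary analyses.
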